**Summary:**

**In study phase 1**, 50 patients with moderate to severe COPD living below 800 m, will be recruited to participate in a randomized cross-over field trial evaluating the hypothesis that exercise capacity during a 4 day sojourn at moderate altitude is reduced in comparison to low altitude. Outcomes will be assessed during 2 days in Zurich (490 m, low altitude baseline), 2 days at Davos Clavadel (1650 m), and 2 days at Davos Jakobshorn (2590 m). The order of altitude exposure will be randomized. The main outcome is the 6 minute walk distance. Additional outcomes are symptom scales, variables from pulmonary function, sleep and vigilance studies, and measures of cardiovascular function. In additional studies 40 patients with precapillary pulmonary hypertension (PH), and 40 patients with interstitial lung disease (ILD) will undergo assessments during 2 days at 490 m, 1 day at 1721 m, and 2 days at 2702 m to evaluate the hypothesis that the 6 minute walk distance is reduced at moderate altitude. If the study locations will not be accessible or will not be appropriate for our needs, the study will take place at different location of comparable altitude. Alternatively, depending on feasibility and logistics, studies will be performed during 2 days in Zurich and during 2 days at only one altitude location, situated between 1650-300 m.

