**In study phase 2**, 50 patients with moderate to severe COPD living below 800 m, will be recruited to participate in randomized, placebo-controlled, double-blind, cross-over trials evaluating the hypothesis that nocturnal supplemental oxygen therapy during a 3-day sojourn at moderate altitude improves exercise performance. After baseline evaluation at 490 m, patients will spend two 3-day periods at altitude (1 day at Samedan, 1721 m, and 2 days at Murtèl Corvatsch, 2702 m) using nocturnal nasal oxygen at a rate of 3 L/Min or placebo oxygen (ambient air at 3 L/Min). The order of treatment modality during the first and second altitude stay will be randomized and treatment periods separated by a 2 week wash-out period at low altitude. The main outcome (6 min walk distance) and the additional outcomes will be the same as in phase 1. Comparisons will be made according to the intention to treat principle among oxygen and placebo oxygen. Alternatively, depending on feasibility and logistics, studies will be performed during 2 days in Zurich and during 2 sojourns of 2 days each at an altitude location situated between 1650-300 m. In additional studies 50 patients with PH, and 50 patients with ILD will be invited to participate in a randomized cross-over trial evaluating the effect of oxygen vs. sham oxygen at 2702m according to a similar protocol as described above for COPD patients. If the study locations will not be accessible or will not be appropriate for our needs, the study will take place at different location of comparable altitude. This protocol has been evaluated by several expert reviewers of the Swiss National Science Foundation and the study will be supported by SNF grant #143875 if approved by the ethics committee.

|                                               |                                                                                                                                                                                                                                                                                                                                                                                                                                                                                                                                                                                                                                               |

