| Main Exclusion Criteria: | 
 
- Unstable condition, COPD exacerbation (change in dyspnea, cough or sputum production which may require a change in treatment). Unstable PH (recent requirement for change in treatment), unstable ILD or exacerbated ILD.
 
- Very severe COPD (FEV1 or diffusing capacity <30% predicted, PaO2 at 490 m <7.3 kPa, PaCO2 at 490 m >6.7 kPa)
 
- Very severe PH, very severe ILD (NYHA 4, diffusing capacity <30% predicted, PaO2 at 490 m <7.3 kPa)
 
- More than mild or poorly controlled cardiovascular disease
 
- Use of drugs that affect respiratory center drive.
 
- Internal, neurologic or psychiatric disease that interfere with protocol compliance including current heavy smoking (>20 cigarettes per day), inability to perform bicycle exercise.
 
- Previous intolerance to moderate altitude (<2600m)
 
- Pregnancy
 
 |
| Study Schedule:          | 05/2013 through 12/2016                                                                                                                                                                                                                                                                                                                                                                                                                                                                                                                                                                                                                                                                                                                                                                                                                                                                                                                                                                            |

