In 2014, the study sites in Davos cannot be used because the Jakobshorn cable car will not be operating. Therefore, we plan to perform altitude studies in the hospital of Samedan (1721m) and at the Corvatsch Murtèl station (2702 m). Both locations provide similar physiologic conditions as those at Davos and the infrastructure is also excellent. For comparison, barometric pressures at Davos Clavadel 1650 m and at Samedan 1721 m are: 623 and 617 Torr, respectively; corresponding values at Jakobshorn 2590 m and Corvatsch Murtèl 2702 m are 554 and 546 Torr, respectively.

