| Day -60 to 0: Subject screening, recruitment, randomization         |                |                |                |
| Sequence A                                                          | Sequence B     | Sequence C     | Sequence D     |
| 490 m, ZH 1-2                                                       | 490 m, ZH 1-2  | 1650m, CL 1-2  | 2590 m, JH 1-2 |
| 1650 m, CL 1-2                                                      | 2590 m, JH 1-2 | 2590 m, JH 1-2 | 1650 m, CL 1-2 |
| 2590 m, JH 1-2                                                      | 1650 m, CL 1-2 | 490 m, ZH 1-2  | 490 m, ZH 1-2  |

| Table 2a. Randomized sequences of altitude exposure in study phase 1 (PH and ILD patients) |                    |
|--------------------------------------------------------------------------------------------|--------------------|
| Day -60 to 0: Subject screening, recruitment, randomization                                |                    |
| Sequence A                                                                                 | Sequence B         |
| 490 m, Zurich 1-2                                                                          | 1721 m, Samedan 1  |
| 1721 m, Samedan 1                                                                          | 2702 m, Murtèl 1-2 |
| 2702 m, Murtèl 1-2                                                                         | 490 m, Zurich 1-2  |

| Table 2b. Randomized sequences of altitude exposure in study phase 1 (PH and ILD patients) if only one altitude location is used |                                        |
|----------------------------------------------------------------------------------------------------------------------------------|----------------------------------------|
| Day -60 to 0: Subject screening, recruitment, randomization                                                                      |                                        |
| Sequence A                                                                                                                       | Sequence B                             |
| 490 m, Zurich 1-2                                                                                                                | Altitude location (at 1650-3000 m) 1-2 |
| Altitude location (at 1650-3000 m) 1-2                                                                                           | 490 m, Zurich 1-2                      |

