## **5 PARTICIPANT ENTRY**

### **5.1 RECRUITMENT**

Patients diagnosed with stable COPD, PH or ILD will be asked to participate. They will be recruited among patients attending the Pulmonary Division University Hospital of Zurich and by advertisements distributed to the Zurich Lung League “Lunge Zürich” and newspapers.

During pre-study screening (recruitment examination), a detailed medical history and review of medical records will be performed to identify any risk factors that may predispose to adverse altitude effects (see exclusion criteria). Pulmonary function, arterial blood gases, resting ECG and a 24 h ambulatory pulse oximetry at the patient’s home will be obtained.

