### **5.3 EXCLUSION CRITERIA**

- Unstable condition and COPD exacerbation defined as a change in the dyspnea, cough or sputum production beyond normal day-to-day variation, acute in onset and which may require a change in treatment; a change in baseline medication within the last 30 days.
- Very severe COPD (i.e. GOLD 4, FEV1<30% predicted), severe gas exchange or hemodynamic impairment: diffusing capacity <30% predicted; hypoxemia requiring oxygen therapy at sea level ( $\text{PaO}_2 < 7.3 \text{ kPa}$ ); hypoventilation ( $\text{PaCO}_2 > 6.7 \text{ kPa}$ ); mean pulmonary artery pressure measured by right heart catheter >40 mmHg or pulmonary artery systolic pressure estimated by echocardiography >50 mmHg.
- Patients with very severe PH, NYHA class 4, unstable PH defined by a change of specific drug therapy within the last 30 days, hypoxemia requiring oxygen therapy at sea level ( $\text{PaO}_2 < 7.3 \text{ kPa}$ ); at 490m.
- Patients with very advanced ILD, NYHA class 4, unstable or exacerbated ILD, hypoxemia requiring oxygen therapy at sea level ( $\text{PaO}_2 < 7.3 \text{ kPa}$ ).

- More than mild or inadequately controlled cardiovascular disease such as uncontrolled systemic arterial hypertension, coronary artery disease, previous stroke; obstructive sleep apnea syndrome (overlap syndrome); pneumothorax in the last 2 months.
- Use of drugs that affect respiratory center drive (sedatives or sleep inducing drugs, morphine or codeine derivatives).
- Internal, neurologic or psychiatric disease that interfere with protocol compliance including current heavy smoking (>20 cigarettes per day), inability to perform bicycle exercise.
- Previous intolerance to moderate altitude (<2600m).
- Exposure to altitudes >1500m for >2 days within the last 4 weeks before the study. Pregnant patients (women potentially capable of childbearing, i.e., who are not yet menopausal and had their last menstrual period less than 12 months ago, who had no hysterectomy, ovariectomy, or surgery to occlude the fallopian tubes, will be tested for pregnancy, on site, at the beginning of the study, by urinary  $\beta$ -HCG-concentration (lifeSign Status hCG Serum/Urine). The urine sample will not be stored.)
- Nursing patients.

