#### **Symptom evaluation**

A complete medical history will be obtained including previous altitude exposure and tolerance, altitude related illness. Physical examination will include weight, height, blood pressure, pulse rate, oxygen saturation by pulse oximetry, cardiac and pulmonary auscultation, evaluation of ataxia by the heel walking test. The COPD assessment test (CAT) will be performed. Perceived exertion will be assessed by the Borg CR10 scale, dyspnea by the modified Medical Research Council dyspnea score, and acute mountain sickness by the environmental symptoms questionnaire cerebral subscore (AMS-c). Sleepiness will be assessed by the Epworth sleepiness scale (ESS) and the Stanford sleepiness scale.

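### The exclusion for previous altitude intolerance stops at 2600 m, 102 m below the scheduled upper site at Corvatsch Murtèl (2702 m)

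*Protocol*

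**What the plan says.** The criterion appears twice with the same limit: in section 5.3, "Previous intolerance to moderate altitude (<2600m"), and in the synopsis list of main exclusion criteria, where "Previous intolerance to moderate altitude" is again followed by the 2600 m figure.

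The 2013 upper site was Jakobshorn (2590 m). Section 3.2 moves the 2014 work to Samedan (1721 m) and Corvatsch Murtèl (2702 m). For PH and ILD patients in phase 1, the synopsis says that they "will undergo assessments during 2 days at 490 m, 1 day at 1721 m, and 2 days at 2702 m", and Table 2a lists "2702 m, Murtèl 1-2" in both sequences. Table 4 places phase 2 COPD patients at Murtèl in each treatment period. PH and ILD patients are to join a phase 2 trial "evaluating the effect of oxygen vs. sham oxygen at 2702m according to a similar protocol as described above for COPD patients".

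Two provisions bear on how altitude history is used. Section 5.1 has medical history and records reviewed "to identify any risk factors that may predispose to adverse altitude effects (see exclusion criteria"). Section 6.1 states: "A complete medical history will be obtained including previous altitude exposure and tolerance, altitude related illness". Section 11.1 says that the inclusion and exclusion criteria are expected to protect participants from clinically relevant harm at altitudes up to 2702 m.

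**The concern.** This is the only exclusion based on how a person has reacted to altitude before. Its limit lies above Jakobshorn but below Murtèl. A candidate who became ill at Murtèl itself, with nothing recorded lower down, would pass the criterion and then be taken back to the altitude of the illness for two days.

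The limit also conflicts with the protocol's own vocabulary. In 5.3 the parenthesis confines moderate altitude to below 2600 m. Section 11.1 uses the same term up to 2702 m, and section 4.2 uses it for the range 1650 to 3000 m.

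What is at stake is participant safety at entry, and whether the risk-benefit statement in 11.1 agrees with the criteria it rests on. The statistical analysis is not involved.

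**Working it through.** **Inputs.** Limit of the criterion: 2600 m (5.3 and synopsis). Upper sites: Jakobshorn 2590 m, Murtèl 2702 m (3.2). Pressures from 3.2: "corresponding values at Jakobshorn 2590 m and Corvatsch Murtèl 2702 m are 554 and 546 Torr, respectively"; Samedan 617 Torr.

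**Altitude.**
- Limit against Jakobshorn: 2600 − 2590 = +10 m, so that site is covered.
- Limit against Murtèl: 2702 − 2600 = 102 m, not covered.

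**Pressure width of the uncovered band.** Linear interpolation between the two stated points:
- Slope: (554 − 546) / (2702 − 2590) = 8 / 112 = 0.0714 Torr per m.
- Pressure at 2600 m: 546 + 102 × 0.0714 = 553.3 Torr.
- Band: 553.3 − 546 = 7.3 Torr.

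**Inspired PO2.** Computed as 0.2095 × (PB − 47). The two constants are standard values assumed here; they are not in the protocol.
- At 2600 m: 0.2095 × (553.3 − 47) = 106.1 Torr.
- At 2702 m: 0.2095 × (546 − 47) = 104.5 Torr.
- Difference: about 1.5 Torr.

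**Does another entry provision close the band?** The other exclusions in 5.3 concern disease severity and stability, cardiovascular and other comorbidity, drugs acting on respiratory drive, compliance, recent altitude exposure, pregnancy and nursing. None acts on past intolerance. The review in 5.1 looks for altitude risk factors but refers back to the exclusion list. The history in 6.1 has no altitude limit, but it collects information and attaches no eligibility consequence to it. The band therefore stays open at entry.

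**What acts afterwards?** Withdrawal criteria (4.2), daily examinations (7.1), and a physician on site with an evacuation plan for Murtèl (9.1). In Table 2a and Table 4 every ascent to 2702 m follows a stay at 1721 m, so examinations and withdrawal rules apply before Murtèl is reached. In 2013, sequences B and D of Table 2 went to 2590 m without a preceding stay at 1650 m.

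**The case against.** The strongest reply is that the mismatch hardly matters. Section 3.2 describes the new locations as physiologically similar to the Davos ones, and the band is worth about 1.5 Torr of inspired PO2. A candidate slips through only with known intolerance inside a 102 m band and none recorded below it. Recalled altitudes are unlikely to be exact to 100 m (a judgement; the protocol gives no figure). An investigator guided by the term moderate altitude, as the protocol uses it elsewhere, would probably exclude such a person anyway. The staged ascent adds a monitored step.

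Most of this stands as an argument about size. It does not make the text right: the written figure governs eligibility, and it disagrees with 11.1. The staged ascent also has limits. Samedan and Murtèl differ by 617 − 546 = 71 Torr, so an uneventful day at 1721 m does not show tolerance at 2702 m. The intermediate day also falls away if only one location is used.

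A reader might be tempted by four stronger inferences that the documents do not support:

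- **That many participants are affected.** The planned numbers at 2702 m show how many people the criterion screens, not how many fall in the band. The protocol gives no rate of previous intolerance.
- **That the gap is really 400 m,** because the one-location option allows up to 3000 m (3000 − 2600 = 400). No site at that ceiling is scheduled. The only one named for the option, above St. Moritz, is at 2044 m, where the present limit is sufficient.
- **That the figure is a proven leftover from Jakobshorn.** The 10 m match suggests it, as do the emergency plan in 7.3, which still names Jakobshorn, and one cell of Table 4, which gives Murtèl as 2590 m. The protocol never states the basis for 2600 m, so this remains an inference.
- **That patients are left unprotected.** The history is taken, and several safeguards apply during the stay.

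**Conclusion.** The point holds as a minor error in an eligibility criterion. The limit is 102 m too low for the scheduled upper site and is inconsistent with the reliance that 11.1 places on the entry criteria up to 2702 m. Known intolerance between 2600 and 2702 m is not a ground for exclusion as written.

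The practical effect is small: about 7 Torr barometric and probably very few candidates, though the number cannot be derived from the protocol. This assumes that the criterion is applied literally, that the two-location schedule is used, and that pressure is close to linear between the two stated sites. The safety gain from correcting it is modest but real, because the remaining safeguards act only after the patient has been enrolled and has left low altitude. It is worth considering at the next amendment and gives no reason to question the design or the analysis.

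**What to change.** In 5.3 and in the synopsis, replace the limit with: *previous intolerance to altitudes up to and including the highest study site used (2702 m at Corvatsch Murtèl)*. Tied to the site, the limit stays correct if another location is chosen, so the one-location option needs no altitude cap on this account.

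The cost is one phrase in two places and the loss of the very few candidates with known intolerance between 2600 and 2702 m. Sample size, outcomes and analysis are unchanged.

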## **6 EVALUATION OF EFFECTS OF ALTITUDE AND OF NOCTURNAL OXYGEN THERAPY**

### **6.1 MEASUREMENTS AND TIMING OF MEASUREMENTS**

The timing of measurements described below is outlined in table 3 (4.2. above).

#### **Exercise tests**

The 6 min walk test and bicycle exercise are performed according to published standards.

During the 6 min walk test, patients will be monitored by a portable pulse oximeter and fill in a 10 point Borg scale at the end of the test. Walk distance, SpO2 and pulse rate at beginning and end of the test will be recorded.

Maximal bicycle exercise will be performed with a progressive ramp protocol to exhaustion. Patients will indicate the perceived exertion on the Borg CR10 scale. Ventilation, gas exchange, oxygen saturation and the ECG will be recorded (ZAN, Oberthulba, Germany). A radial artery blood sample will be drawn at rest and during maximal exercise and analyzed on site immediately by a blood-gas analyser (RAPIDPOINT 405, Siemens, Bad Nauheim, GE). Data will be stored in anonymized format using a unique participant number. No blood will be stored for further analysis.

#### **Symptom evaluation**

A complete medical history will be obtained including previous altitude exposure and tolerance, altitude related illness. Physical examination will include weight, height, blood pressure, pulse rate, oxygen saturation by pulse oximetry, cardiac and pulmonary auscultation, evaluation of ataxia by the heel walking test. The COPD assessment test (CAT) will be performed. Perceived exertion will be assessed by the Borg CR10 scale, dyspnea by the modified Medical Research Council dyspnea score, and acute mountain sickness by the environmental symptoms questionnaire cerebral subscore (AMS-c). Sleepiness will be assessed by the Epworth sleepiness scale (ESS) and the Stanford sleepiness scale.

## **Pulmonary function tests**

Spirometry, lung volumes, diffusing capacity, maximal inspiratory, expiratory and sniff nasal pressures are measured according to published standards (Vmax, SensorMedics). Ambulatory nocturnal pulse oximetry will be performed with a miniaturized device (Minolta 300i, Konica Minolta Sensing Inc.) placed at the wrist and a finger clip. Arterial oxygen saturation is recorded over the course of a night during which the patient sleeps at home. Data are downloaded in the next morning and the mean nocturnal oxygen saturation and the number of dips >3% related to the time the patient spent in bed will be determined.

## **Reaction, vigilance and psychomotor performance**

The tests as described below provide multiple, well defined parameters of psychomotor performance. They will be performed in a quiet room with subjects wearing sound protective ear covers. The light in the room will be dimmed.

Psychomotor Vigilance Test (PVT): Vigilance will be assessed by the Psychomotor Vigilance Test (PVT) which is sensitive for effects of sleep restriction/disturbance and hypoxia. As described by Dinges et al the PVT measures the reaction time to a visual stimulus (LED) presented in variable intervals between 1 to 10 s over a period of 10-15 min. The subjects respond by pressing a button on a hand-held device (Stowood Scientific Instruments Ltd., Oxford).

Trail making test A: This Trail making test A provides information about executive functions and mental flexibility. On a paper sheet are numbers from 1 to 90. Before starting the test, the patient has to draw 1 of 4 sheets with differently randomized numbers. The patient has to connect the numbers from 1 to 90 by drawing a line from number to number. The next higher number is always neighboring the previous number.

Vestibular-ocular reflex: The vestibular-ocular reflex stabilizes gaze during head rotations with equal eye rotations to the opposite direction. Hypoxia will impair this reflex causing balance problems and oscillopsia (jiggling vision) in more severe cases. This will lead to fast correction movements of the eyes to refocus the target (catch-up saccades). The video head impulse test is performed in the sitting patient focusing on a target straight ahead. His head will be turned in approximately 20 small, unpredictable movements to both sides by the examiner (10-15°, 150-200°/s). The patient wears a light video-goggle (ICS Impulse, GN Otometrics, Denmark) which will record the movements of his head and his eyes. The gain of the vestibulo-ocular reflex as well as timing and amplitude of the catch-up saccades will be analyzed. Saccade metrics including amplitude, latency and timing are sensitive markers in response to hypoxia. In addition, the ability to generate anti-saccades will likely be impaired.

